#### Event ascertainment and adjudication

Potential endpoint events will be identified through 1) in-hospital electronic medical records and discharge databases, and 2) standardized follow-up contacts at 2, 4, and 12 weeks after discharge. For hospitalizations outside the study center, participants or family members will be asked to provide discharge summaries and key supporting documents (admission/discharge notes, medication records, imaging/laboratory reports). All suspected events will be adjudicated by an independent Clinical Events Committee blinded to treatment allocation and BCM data, using prespecified definitions. Disagreements will be resolved by consensus or a third adjudicator.

After investigators submit the relevant case-report documentation, independent, blinded medical adjudicators contracted for the study will determine 3-month cardiovascular mortality, all-cause mortality, number of heart-failure hospitalizations, time to first heart-failure admission, and any associated questionnaires.

The Kansas City Cardiomyopathy Questionnaire (KCCQ) will be administered at baseline by an independent, blinded assessor on site; at the 3-month follow-up, the same instrument will be completed via telephone by an independent, blinded assessor.

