### Blinding

This is an open-label trial with blinded endpoint adjudication. An independent Clinical Events Committee (CEC), whose members are blinded to treatment allocation, patient identity, and all fluid load data, will adjudicate all potential primary and secondary endpoint events according to pre-specified, standardized definitions.

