#### Endpoint definitions

Heart-failure rehospitalization is defined as an unplanned hospital admission lasting ≥24 h with a primary diagnosis of heart failure, accompanied by worsening signs/symptoms of congestion and requiring intensification of HF therapy (e.g., intravenous loop diuretics and/or vasoactive therapy). Planned admissions for elective procedures without clinical deterioration are not counted as endpoint events. All-cause death is defined as death from any cause occurring within 90 days after discharge.

Hypotension is defined as a systolic blood pressure <85 mmHg during hospitalization requiring reduction in diuretic therapy or initiation of vasopressor support.

Acute kidney injury (AKI) is defined as the occurrence of any one of the following: 1) Serum creatinine increases by ≥0.3 mg/dl (≥26.5 μmol/L) within 48 h; 2) Creatinine rises to >1.5 times baseline, indicating known or presumed renal dysfunction occurring within 7 days; 3) Urine output <0.5 ml/(kg·h) for at least 6 consecutive hours.

Electrolyte disturbances: 1) Hyperkalemia is defined as any serum potassium level >5.5 mmol/L observed during hospitalization or follow-up. 2) Hypokalemia is defined as any serum potassium level <3.5 mmol/L observed during hospitalization or follow-up. 3) Hyponatremia is defined as any serum sodium level <130 mmol/L observed during hospitalization or follow-up. Hypernatremia is defined as any serum sodium level >150 mmol/L observed during hospitalization or follow-up.

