### Strengths and limitations of the study

This trial represents the first randomized controlled design to validate the efficacy and safety of the precision volume management strategy in patients with acute decompensation of chronic heart failure. Its core innovation lies in establishing a structured, closed-loop “measure–assess–adjust–reassess” pathway, which integrates the quantitative threshold of fluid overload (overhydration, OH) measured by BIA into daily clinical decision-making. This protocol aims to enable precise, individualized, and standardized volume control, thereby optimizing diuretic therapy.

However, several limitations should be acknowledged. First, due to the nature of the intervention, which necessitates that treating physicians actively view BIA data to adjust diuretic dosages, blinding of the clinical team is not feasible. This open-label design may theoretically introduce performance bias. To mitigate this, the primary endpoint comprises objective “hard” outcomes (all-cause mortality and heart failure rehospitalization) that are less susceptible to subjective influence. Furthermore, all clinical events will be adjudicated by an independent CEC blinded to treatment allocation to ensure the integrity of the results.

Finally, the single-center design of this study may limit the external validity and generalizability of the findings to other populations or healthcare settings. Consequently, future multicenter randomized trials will be essential to confirm and extend our conclusions.

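### Blinded adjudication covers how submitted events are classified, not who is admitted or which admissions are submitted, so the protection claimed for HF rehospitalisation is only partial

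*Protocol article*

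**What the plan says.** The Blinding section sets the design: "This is an open-label trial with blinded endpoint adjudication". It describes a Clinical Events Committee (CEC) blinded to allocation, patient identity and fluid data, which "will adjudicate all potential primary and secondary endpoint events according to pre-specified, standardized definitions".

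The section Event ascertainment and adjudication describes how events reach that committee. "Potential endpoint events will be identified through 1) in-hospital electronic medical records and discharge databases, and 2) standardized follow-up contacts". The schedule for these is weeks 2, 4 and 12. For admissions elsewhere, "participants or family members will be asked to provide discharge summaries and key supporting documents". Then "All suspected events will be adjudicated by an independent Clinical Events Committee blinded to treatment allocation and BCM data". A further paragraph adds: "After investigators submit the relevant case-report documentation, independent, blinded medical adjudicators contracted for the study will determine" mortality, HF hospitalisations and time to first HF admission. A blinded assessor is specified for the KCCQ, including the 3-month telephone call. Nothing is said about the blinding of those who search the records or make the event contacts.

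Endpoint definitions counts an HF rehospitalisation only for "an unplanned hospital admission lasting ≥24 h with a primary diagnosis of heart failure", with worsening congestion and intensified HF therapy.

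Strengths and limitations concedes that the clinical team cannot be blinded. It answers this by describing both components of the primary endpoint as hard outcomes "that are less susceptible to subjective influence", and by relying on the blinded CEC for the integrity of the results.

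**The concern.** Two separate steps can carry open-label bias into an HF-rehospitalisation endpoint. The first is care: whether a patient is admitted, stays 24 h, is labelled as HF and has therapy stepped up. The second is capture: whether that admission is recognised as a possible event and its papers are submitted. A blinded committee works after both. It can reject a submitted event that fails the definition. It cannot restore an admission that did not happen, a stay that ended before 24 h, or an admission that never reached it.

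If either step differs by arm, the primary hazard ratio is biased and adjudication as written would not show it. The limitations section names only performance bias, calls it theoretical, and treats the two components of the composite as equally protected.

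**Working it through.** **Step 1. Set the protection against each element of the endpoint.**

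| Element | Who decides or acts | Does blinded adjudication reach it? |
|---|---|---|
| Death from any cause | Nobody's judgement | Little to protect; the claim is reasonable |
| Decision to admit | Treating clinician; blinding not stated | No |
| Stay of at least 24 h | Treating clinician; blinding not stated | Duration can be verified, the decision cannot be undone |
| HF as primary diagnosis | Treating clinician, then CEC | Yes, for submitted files |
| Congestion and intensified therapy | Treating clinician, then CEC | Documentation can be checked, the treatment decision cannot be undone |
| Recognising the admission as a suspected event | Whoever searches records or makes contacts; blinding not stated | No |
| Submitting the papers | Investigators; for outside admissions, participants or family supply them | No |

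The committee's work covers classification. Admission, stay and selection lie before it.

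**Step 2. Inputs for an illustration of size.**
- Control event rate at 3 months: 24.9% (Sample size).
- Planned relative reduction: 20%, giving 24.9% × 0.80 = 19.9%, as the protocol states.
- Participants per group before attrition: 242 (Sample size), taken as printed. This point does not depend on how that figure was derived.
- Assumed: no true effect, so 24.9% in both arms.
- Assumed: HF readmissions are a share s = 60% to 90% of first events. The document gives no split.
- Assumed: a fraction d = 10% to 20% of intervention-arm HF readmissions is not admitted, does not reach 24 h or is not submitted, with no loss in the control arm.

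**Step 3. Apparent effect.** Observed intervention rate = 24.9% × (1 − s × d), so the apparent relative reduction is s × d.

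| s | d | Observed rate | Apparent reduction | Chance of a significant false benefit, 242 per group |
|---|---|---|---|---|
| 60% | 10% | 23.4% | 6% | 5.7% |
| 60% | 20% | 21.9% | 12% | 11.8% |
| 80% | 10% | 22.9% | 8% | 7.4% |
| 80% | 20% | 20.9% | 16% | 17.9% |
| 90% | 10% | 22.7% | 9% | 8.4% |
| 90% | 20% | 20.4% | 18% | 21.7% |

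The last column uses a two-sided 5% comparison of two proportions as a stand-in for the log-rank test. The nominal chance in that direction is 2.5%.

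**Step 4. Scale in events.** The planned difference is 242 × 0.249 − 242 × 0.199 = 60.3 − 48.2, about 12 events. To imitate all of it with no true effect, d would have to be 0.20/s: 33% at s = 60% and 22% at s = 90%.

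**The case against.** The strongest reply is that the plan has more safeguards than a simple investigator gate.

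- **Event finding.** Records and discharge databases are searched, both arms have the same contacts, and the Blinding section sends all potential events to the CEC. This stands. A reader might infer that the committee sees only what unblinded staff choose to send; the document does not say that. It is silent on whether those who find events are blinded, and silence is not a statement that they are unblinded. What remains is that somebody must decide which admissions are suspected events, and no blinding is stated for that step.
- **Clinicians at readmission.** The intervention is confined to the index stay, research personnel outside routine care take the measurements, and the results stay out of the electronic medical record. A clinician weeks later, or at another hospital, need not know the arm. This also stands. It makes bias less likely without excluding it in a single-centre, open-label trial.
- **Oversight.** Supporting admission records are entered, data managers reconcile key variables, and on-site review takes place at least every 3 months. These help with capture but not with admission decisions.
- **Tone of the claim.** The wording is comparative and sits in a limitations section. That is fair, and it is why the protection should be called partial, not absent.
- **Article format.** Referral triggers may be set out in a fuller protocol or committee charter. Their absence here is therefore not the point. The point is that the article states an intake rule and makes a claim that the rule cannot carry.
- **Invented inputs.** The loss fractions and the HF share are assumptions, and the result is proportional to them. Loss in the control arm would offset or reverse the bias. This is accepted; the figures show sensitivity, not a forecast.

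**Conclusion.** The point holds in a limited form. Blinded adjudication protects classification. It does not protect the decision to admit, the length of stay or the selection of admissions for submission. Protection is reasonable for all-cause death and partial for HF rehospitalisation, so the limitations section claims too much in giving both the same assurance.

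On the stated assumptions (no true effect, 24.9% in both arms, HF share 60% to 90%, one-sided loss 10% to 20%) the apparent relative reduction is 6% to 18%, and the chance of a significant false benefit at 242 per group is about 6% to 22%. The document supplies neither the HF share nor any loss rate.

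Two stronger readings are not supported. One is that the safeguard fails altogether: the CEC is blinded, applies fixed definitions and can reject unsupported events. The other is that HF rehospitalisation is known to be the main component of the composite: this is plausible, but no split is given. The design remains usable; the intake rule and the claim should be corrected.

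**What to change.** 1. In Event ascertainment and adjudication, refer to the CEC every death and every unplanned admission of any cause within 90 days, as found by the record and database search and the scheduled contacts. The CEC assigns the primary cause from redacted records. This removes the filter of suspicion before blinded review.
2. Add all-cause unplanned rehospitalisation or death within 90 days as a supportive analysis. It does not depend on the HF label, so a result that differs from the primary one would expose selective labelling.
3. Have the blinded assessor who makes the week-12 KCCQ call also ask scripted event questions. This leaves the 2- and 4-week contacts unchanged.
4. In Strengths and limitations, confine the claim of lower susceptibility to all-cause death, and state that adjudication does not remove bias in admission decisions or event capture.

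A composite that also counts intravenous-diuretic visits under 24 h would address the length-of-stay threshold. It should be added only if those visits are already recorded, which the article does not show.

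The cost is revised wording in the protocol and any committee charter, a short addition to one telephone call, and more admission files for the existing committee to read. No further patients or visits are needed. Recruitment is under way, so the change is best made soon, through the usual ethics approval.

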### Data collection and management

Data will be entered and stored using a secure EDC system with built-in real-time validation rules. Logical checks and predefined ranges for key variables will be applied to minimize data entry errors. The EDC system will automatically generate visit schedules and allowable time windows for each enrolled participant, facilitating continuous and standardized data management.

#### Data entry

Following each subject visit, the investigator or authorized research staff will log into the EDC system and enter data based on medical records or the paper-based Case Report Form (CRF) completed during the visit, including laboratory test reports and all relevant supporting documents (e.g., admission records), to complete the electronic Case Report Form (eCRF) entry.

#### Central data-quality review

Data managers will perform routine quality control procedures, including logic checks, consistency validation, and targeted reconciliation of key variables against the CRF, to ensure data completeness and accuracy. Additionally, real-time monitoring of data collection and entry timelines will be conducted to maintain a high-fidelity study database.

#### Feedback and monitoring for clinical research center

Data verification reports will be periodically generated and provided to the clinical research center, summarizing data entry timeliness and the occurrence of missing or inconsistent data. The data collection process will undergo regular independent review, with particular attention to data completeness and quality. Any identified issues related to data collection practices will be communicated to the center for appropriate follow-up action in accordance with the study's quality management procedures.

#### Data confidentiality

All personnel (site investigators, project-management staff, and third-party vendors) are bound by strict confidentiality agreements. Paper CRFs and source medical records remain under lock at the participating sites; copies of SAE and clinical-event source documents retained by the coordinating office are stored in locked cabinets within secure, access-controlled rooms. If upload via the study web portal is required, files reside in a non-public directory reachable only through the internal project site. All database access is username/password-protected, passwords are encrypted at rest.

#### Data sharing

Deidentified participant data will be available upon reasonable request from the corresponding author, beginning 6 months after publication and for 3 years thereafter. Requests must specify the scientific rationale, variables sought, intended analyses, and analytical plan, and will be reviewed by the steering committee prior to approval and secure transfer under a data-use agreement.

### Statistical analysis

Analyses will be performed with SPSS 26.0 (SPSS Inc., Chicago, IL) and R 4.2.1 (R Foundation, Vienna). All analyses will follow the intention-to-treat principle, with participants analyzed according to the randomized assignment. Baseline characteristics will be summarized using mean (SD) or median (IQR) for continuous variables and counts (%) for categorical variables.

The primary endpoint (time to first occurrence of heart-failure rehospitalization or all-cause death within 3 months) will be analyzed using Kaplan–Meier methods and compared between groups using the log-rank test. Treatment effect will be estimated using Cox proportional-hazards models, reporting hazard ratios (HRs) with 95% confidence intervals. The proportional-hazards assumption will be assessed using Schoenfeld residuals. A prespecified adjusted Cox model will include clinically relevant baseline covariates (e.g., age, sex, BMI, LVEF, NYHA class, baseline NT-proBNP). Baseline diuretic dose (expressed as furosemide-equivalent dose) will be compared between groups and included as a covariate in adjusted analyses if clinically relevant imbalance is observed.

For time to first heart-failure rehospitalization, death will be treated as a competing event; Fine–Gray subdistribution hazard models will be used as a supportive analysis. Cardiovascular and all-cause mortality will be analyzed using KM/log-rank and Cox models as appropriate.

The total number of heart-failure rehospitalizations within 3 months will be analyzed using a negative binomial regression model (offset by follow-up time), reporting incidence rate ratios (IRRs) with 95% CIs. As a sensitivity analysis, a recurrent-event time-to-event model (e.g., Andersen–Gill) may be applied. Deaths occurring during the index hospitalization will be recorded as safety outcomes but will not be included in the primary time-to-event analysis, which focused on post-discharge events.

Changes in weight, NT-proBNP, and KCCQ scores over time will be evaluated using linear mixed-effects models with random participant intercepts, incorporating all available repeated measurements.

Safety endpoints (acute kidney injury, hypotension, electrolyte imbalance) will be summarized as counts (%) and compared using *χ*² or Fisher's exact tests.

The primary endpoint will be tested at a two-sided alpha level of 0.05. All secondary endpoints will be analyzed as exploratory; no formal multiplicity adjustment will be applied. For secondary and safety outcomes, effect estimates with 95% confidence intervals will be reported and interpreted cautiously.

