### Sample size

The sample size was calculated to test the superiority of a BIA-guided precision fluid management strategy over standard empirical diuretic therapy. Based on previous data, the 3-month incidence of the composite outcome of heart failure rehospitalization or all-cause mortality in the control group was assumed to be 24.9% (1). We hypothesized a 20% relative risk reduction with the intervention, corresponding to an expected event rate of 19.9% in the intervention group.

With a significance level of 0.05, a power of 80%, and a 1:1 randomization ratio, a total of 242 participants per group were required. Allowing for a 10% attrition rate, the final target sample size was increased to 269 participants per group, yielding a total sample size of 538. Sample size calculations will be performed using PASS software.

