### Randomization and allocation concealment

Participants will be randomly allocated in a 1:1 ratio using a computer-generated randomization sequence with variable block sizes (e.g., 4, 6, or 8). The randomization list will be prepared by an independent statistician and concealed from investigators involved in enrollment and clinical management. Allocation concealment will be ensured via a centralized electronic randomization module within the electronic data capture (EDC) system. Randomization will be performed only after eligibility confirmation and informed consent; prior to randomization, investigators responsible for screening and enrollment will have no access to the allocation sequence or the upcoming assignment.

Given the single-center design and relatively large sample size, stratified randomization was not implemented. Baseline characteristics, including diuretic exposure, will be assessed for balance between groups. If clinically meaningful imbalance is observed, adjusted analyses will be performed.

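### Baseline diuretic dose enters the adjusted Cox model only if imbalance is observed, a trigger without a threshold that also conflicts with the unconditional adjusted model planned in the same article

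*Protocol article*

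**What the plan says.** Protocol article, Statistical analysis. The primary endpoint "will be analyzed using Kaplan–Meier methods and compared between groups using the log-rank test", and "The primary endpoint will be tested at a two-sided alpha level of 0.05". Cox models supply the hazard ratios. The next step is unconditional: "A prespecified adjusted Cox model will include clinically relevant baseline covariates (e.g., age, sex, BMI, LVEF, NYHA class, baseline NT-proBNP", and so on. The sentence after it treats one covariate differently. Baseline diuretic dose, in furosemide equivalents, is compared between the arms and "included as a covariate in adjusted analyses if clinically relevant imbalance is observed".

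Protocol article, Randomization and allocation concealment. The section reports that "stratified randomization was not implemented", says that balance at baseline, diuretic exposure included, will be examined, and continues: "If clinically meaningful imbalance is observed, adjusted analyses will be performed".

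Neither section says how large an imbalance must be or by what measure it is judged. The article also does not say whether the unadjusted or the adjusted hazard ratio is the main effect estimate.

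**The concern.** There are two difficulties.

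First, the sections disagree. One promises an adjusted model whatever the baseline table shows; the other makes adjusted analyses follow from imbalance. A reader cannot tell whether the adjusted model is always fitted, or which covariates it will contain.

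Second, imbalance is the wrong criterion. With sound randomisation any baseline difference is chance. What makes a covariate worth including is how strongly it predicts outcome, and that can be settled before any data are seen. If diuretic dose is prognostic, it belongs in the model when the arms look balanced too; if it is not, an imbalance in it does no harm.

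At stake are the reproducibility of the adjusted hazard ratio and a modest amount of power. Two analysts following the text in good faith could report different adjusted estimates.

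**Working it through.** **1. The rules side by side.**

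| Section | Adjusted model fitted? | Diuretic dose in it? | Threshold |
|---|---|---|---|
| Statistical analysis | Always | Only on imbalance | None |
| Randomization and allocation concealment | On imbalance | Named as a balance check | None |

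**2. How far the missing threshold matters.** For a standardised covariate with 269 per arm (Sample size section), the chance difference in means has standard error √(2/269) = 0.086 SD. Two assumed thresholds:
- 0.1 SD: 0.1/0.086 = 1.16, two-sided tail probability about 25%.
- 0.2 SD: 0.2/0.086 = 2.32, two-sided tail probability about 2%.

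Under perfect randomisation, then, diuretic dose would enter in about one trial in four or one in fifty, depending on a number that the text does not give.

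**3. Background power.** The plan states no figure for the effect of adjustment; its only related figure is the sample size: "With a significance level of 0.05, a power of 80%, and a 1:1 randomization ratio, a total of 242 participants per group were required". For 24.9% against 19.9% (mean 22.4%), two-sided 0.05:

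n = [1.96·√(2·0.224·0.776) + 0.842·√(0.249·0.751 + 0.199·0.801)]² / 0.05² ≈ 1,091 per group.

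The stated 242 is not reproduced, and power at 242 per group is about 26%. That is a separate and larger problem. It is given here only because it explains why the powers below are low.

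**4. Simulation at the evaluable size.** Inputs from the Sample size section: 484 patients (242 per group) and control risk 24.9%. Assumptions: exponential event times, one standard-normal prognostic covariate with log-HR 0.3, 0.5 or 0.8 per SD, a trigger of 0.1 SD, and a conditional HR of 0.7765, close to ln(1 − 0.199)/ln(1 − 0.249) = 0.775. There were 2,000 runs per scenario, with Wald tests from Cox models.

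| Log-HR per SD | Quantity | Never adjusted | Always adjusted | Adjusted only on imbalance |
|---|---|---|---|---|
| 0.3 | Power | 24.3% | 24.9% | 24.3% |
| 0.5 | Power | 24.3% | 25.2% | 24.1% |
| 0.8 | Power | 21.6% | 26.4% | 22.5% |
| 0.3 | Type I error | 4.8% | 5.0% | 5.1% |
| 0.5 | Type I error | 4.2% | 4.3% | 3.9% |
| 0.8 | Type I error | 4.5% | 4.8% | 4.0% |

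The Monte Carlo standard error is √(0.05·0.95/2000) ≈ 0.5 points for type I error and √(0.25·0.75/2000) ≈ 1 point for power. The methods share the same simulated data, so their differences are steadier than that, but a gain of 0.6 points is still close to nothing.

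**5. A second simulation at full enrolment.** With 538 patients, log-hazard SD 0.6 to 0.9, the same trigger, 3,000 runs and the plan's two event rates, power was 29%–30% unadjusted, 29%–30% triggered and 32%–34% always adjusted. Type I error was 0.038–0.042 for the triggered rule and 0.046–0.048 for always adjusting.

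**6. Reading.** Always adjusting beats never adjusting by 0.6 (24.9 − 24.3) to 4.8 points (26.4 − 21.6) in the first simulation, and by about 2 (32 − 30) to 5 (34 − 29) in the second. The triggered rule captures little of this. Its type I error is at nominal or slightly below.

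**7. What was not modelled.** Both simulations switch a whole prognostic covariate in or out. Under the Statistical analysis section the named covariates stay in and only diuretic dose switches. The gain from that one variable, given the others, was not estimated; the documents hold no figure for its prognostic strength.

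**The case against.** The strongest reply is that the plan already does most of what is asked. The Statistical analysis section lists prognostic covariates for an adjusted model that does not depend on imbalance. The sentence in the randomisation section can be read as offering further analyses, since it does not say that adjustment happens only on imbalance. An unadjusted log-rank test with an adjusted Cox model beside it is a standard, valid design. Closing the list of example covariates and setting thresholds are ordinary work for a statistical analysis plan, which is not shown.

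Much of this stands. An open list alone would not be a finding. What remains is a written rule: an unseen analysis plan would have to override it, not merely complete it.

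A reader might infer more than the text supports:
- That all adjustment hangs on imbalance. It does not; in the Statistical analysis section only diuretic dose does.
- That the trial's type I error is inflated. The primary log-rank test is fixed and unadjusted, and the triggered rule was near nominal or mildly conservative in simulation.
- That an open-label team will choose after seeing outcomes. The documents do not say who judges imbalance or when, and it can be judged from baseline data alone.
- That unstratified randomisation leaves adjustment as the only protection. Randomisation itself protects validity.

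**Conclusion.** The point holds in a limited form. The two sections conflict, and the rule for diuretic dose makes the adjusted hazard ratio data-dependent for a reason that has no bearing on prognosis. The validity of the primary test is not in question.

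The size is modest: about 0.6 to 5 power points for always adjusting over not adjusting, on a base of roughly 22% to 30%. This rests on an assumed covariate strength (log-HR 0.3 to 0.9 per SD), exponential times and an assumed trigger of 0.1 SD. It is better taken as an upper guide than as the effect of diuretic dose alone, because the other covariates are already in the model. Adjustment does not repair the trial's low power.

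It would go too far to conclude that the adjusted Cox model must replace the log-rank test as the primary test. That is an option with a case on both sides, and the documents do not require it.

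**What to change.** Change three things in the protocol and carry them into the analysis plan:

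1. Delete the imbalance triggers in both sections. Baseline characteristics can still be tabulated by arm.
2. Always fit the adjusted Cox model with a closed list: log NT-proBNP, LVEF, NYHA class, age, sex, BMI and baseline furosemide-equivalent dose. Keep continuous variables continuous. Impute missing baseline values, as the Missing data handling section already provides, so that nobody is dropped.
3. State in advance whether the adjusted or the unadjusted hazard ratio is the main effect estimate, and report the other as supportive. The log-rank test may remain the primary test.

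The cost is wording and an amendment. All seven variables are already named in the plan, and recruitment is still under way, so the change can be made before the arms are compared. One minor downside is that the adjusted hazard ratio is conditional on the covariates, not marginal, and is slightly harder to explain.
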